#### Cost-effectiveness analysis

Costs and cost-effectiveness will be assessed for the follow-up point (24 weeks) using a standard economic analysis framework, shown to be appropriate in an earlier trial [59]. A unit cost will be sought for each service used, including SBHC, by young people in the ETHOS trial and recorded on the database (e.g. [47, 59, 60]. To facilitate estimation of the full costs of SBHC, additional data will be collected from SBHC counsellors (for example, on time spent travelling, liaising with professionals, or in supervision) and from those organising the counsellor service. The amount of each service used by each young person will be multiplied by the appropriate unit cost and summed to arrive at a total support cost per young person for the baseline and follow-up (24 weeks) time points.

Descriptive statistics (frequencies, percentages, means, range, SD) will be used to compare the support packages and costs at each time point for each group. Service and support costs will be identified by funder, including those supports and services provided and funded by the school. Care will be taken to identify any systematic cost differences between locations (schools) as the local array of services may differ, leading to variations in access and, therefore, use. Cost and outcome data will be compared over time and between the SBHC and PCAU group and incremental cost-effectiveness ratios (ICERs) calculated using the change in primary outcome (YP-CORE). In the event of the SBHC group having both higher costs and generating improved outcomes, the current approach is to estimate cost-effectiveness acceptability curves (CEACs). The net monetary benefit for the outcome measures will be calculated and the proportion of bootstrapped estimates of the group difference favouring SBHC will be plotted with corresponding values of willingness to pay.

### Risk procedures and reporting of adverse events (AEs)

Written protocols for managing risk, and monitoring and reporting AEs and serious adverse events (SAEs) is followed for all trial participants throughout the trial (from the point of enrolment into the trial, to the follow-up/24-week time point). An adverse event (AE) is defined as any negative psychological, emotional or behavioural occurrence, or sustained deterioration in a research participant. In the current trial, we have included arrest by police; running away from home; excluded from family home; school exclusion; significant decrease in school attendance; significant deterioration in behaviour, including threatening violence, exhibiting violent behaviour or serious injury to another person, exposure to violence or abuse; significant increase in emotional difficulties; self-harm (if not a presenting issue), or escalating self-harm (when it is a presenting issue); a complaint made against the counsellor, or an issue with the counsellor, resulting in discontinuation of counselling; suicidal ideation; suicidal intent; hospitalisation due to drugs or alcohol, or for psychiatric reasons; and death, including suicide.

An Adverse Events Reporting Form is used by all individuals in contact with participants, who are trained to recognise and respond, in an ethical and timely way, to risk and any issues relating to safeguarding. The overall safety of participants is the responsibility of the trial’s chief investigator (CI). However, in practice the CI relies on all research staff, counsellors, supervisors and school staff to ensure that AEs are identified and addressed in an appropriate and timely manner. Thus, safety is a shared responsibility. Individuals completing the form are asked to consider whether the AE is serious, defined as any AE which is life threatening or results in death, and whether it may be a result of participating in the trial. The severity of each AE is also assessed, according to its intensity, duration and the degree of impairment to the young person (or, when relevant, another person such as in case of risk to others). Severity is graded as ‘mild’, ‘moderate’, ‘severe’, ‘very severe’, or ‘extremely severe’.

The CI has responsibility for reviewing and signing the AE Reporting Forms, for ensuring that the relevant school staff member is aware of the occurrence of any AEs or SAEs at their school; and the ETHOS clinical lead (CL) in instances where the AE or SAE has occurred in a participant in the SBHC group. The CI is also responsible for reporting the AE or SAE to the Chair of the Data Monitoring and Ethics Committee (DMEC) (see ‘Governance and oversight’ below). In the case of SAEs, or those deemed related to participating in the trial, expedited reporting procedures are followed, which includes a reporting timeframe of one week from receipt of the AE Reporting Form.

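### Only fatal or life-threatening events count as serious, so a listed hospitalisation that is neither is not an SAE and, unless judged trial-related, has no one-week report

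*Protocol article*

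**What the plan says.** All the governing text is in the protocol article, under Risk procedures and reporting of adverse events (AEs).

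- **AE list.** Among many event types, some behavioural and some clinical, it includes "hospitalisation due to drugs or alcohol, or for psychiatric reasons; and death, including suicide".
- **Seriousness.** The person completing the form considers whether the event is serious, "defined as any AE which is life threatening or results in death".
- **Relatedness.** The same person considers the event's link to the trial, "and whether it may be a result of participating in the trial".
- **Severity.** "The severity of each AE is also assessed, according to its intensity, duration and the degree of impairment to the young person". There are five grades. The article links none of them to seriousness or to the speed of reporting.
- **Routine reporting.** The chief investigator reviews and signs the forms and must report each AE or SAE to the DMEC Chair. No interval is given for this.
- **Expedited reporting.** "In the case of SAEs, or those deemed related to participating in the trial, expedited reporting procedures are followed". The time allowed on this route is one week, counted from when the form is received.

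Three other sections bear on the point. Blinding says that providers and assessors cannot be masked. Analysis of clinical effectiveness plans a comparison of AE frequency by allocation. Governance and oversight gives the DMEC the task of looking for safety problems in accruing data.

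**The concern.** A psychiatric admission, or one for drugs or alcohol, is a discrete event that can be verified. In this population it would be an important sign of deterioration: participants are 13 to 16 years old with moderate to severe distress, and those considered at risk of serious harm at assessment are not enrolled. The protocol recognises such admissions as worth recording, yet admission alone gives them neither the SAE label nor the faster route.

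What is at stake is how soon the DMEC learns of these events and how clearly it can see them. Without the SAE label, whether an admission is expedited depends on a judgement of relatedness. That judgement is made on a form completed by everyone in contact with participants, including counsellors, assessors and pastoral care staff, and some of these people know the allocation. Under the ordinary AE label, an admission sits beside event types such as reduced attendance and school exclusion. A few admissions could be hard to pick out of an overall AE frequency.

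**Working it through.** No arithmetic applies: the point concerns a definition and a reporting rule, and the article gives no event rates. The check is to apply the article's rules to one event that it lists, "hospitalisation due to drugs or alcohol, or for psychiatric reasons", under each combination of the two judgements on the form.

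**Rules used**

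1. SAE if life threatening or fatal.
2. Expedited (one week from receipt of the form) if an SAE, or if deemed related to participation.
3. Reported to the DMEC Chair in every case.

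| Life threatening or fatal? | Deemed related? | SAE? | One-week report? | Reported to DMEC Chair? |
|---|---|---|---|---|
| Yes | Yes | Yes | Yes | Yes |
| Yes | No | Yes | Yes | Yes |
| No | Yes | No | Yes | Yes |
| No | No | No | No | Yes, no timeframe stated in the article |

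**Reading the table**

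- The SAE label is missing in the third and fourth rows, that is, for every listed admission that is neither life threatening nor fatal.
- The one-week report is missing only in the fourth row, where the admission is also not deemed related.
- The severity grade changes no row. An admission in the fourth row stays there even at the highest of the five grades, because neither rule refers to the grade.
- Between the third and fourth rows only the relatedness judgement differs, so for an admission that is not life threatening or fatal that judgement alone decides whether the DMEC Chair is told within a week. Under Blinding, providers and assessors know the allocation, and they are among those who complete the form.

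**What the DMEC still sees.** The fourth-row event still goes to the DMEC Chair. It falls within the accruing data that the committee reviews and within the planned AE comparison by arm. What is missing is the SAE classification and the deadline.

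**The case against.** The case on the other side is substantial.

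**Oversight remains.** Each AE form is reviewed and signed by the chief investigator, the relevant school staff member is made aware of the event, and the DMEC Chair is told. The DMEC also receives closed reports from the trials unit, and its Chair may ask for more. This stands, and it limits the point to classification and timeliness.

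**The article is a condensation.** It refers to separate written procedures for AEs and SAEs that are not shown and may set a deadline for ordinary AEs. This stands as far as the missing deadline goes. It does not answer the point about the definition or the expedited trigger, both of which the article states outright.

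**Stronger readings that the article does not support**

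- *That all listed hospitalisations miss both the SAE count and the one-week report.* A life-threatening or fatal admission is an SAE, and one deemed related is expedited in any case.
- *That the article contradicts itself.* Listing an event as an AE without making it automatically serious is consistent, and the article cites no outside standard of seriousness that it fails to meet. The definition is narrow, not inconsistent.
- *That expedited reports will be fewer in the pastoral care arm.* The form asks whether the event may result from taking part in the trial, which is wider than whether counselling caused it and applies to both arms. Unblinded judgement leaves room for a difference, but the article documents neither its direction nor its size.
- *That a final SAE table will leave these events out.* The article mentions no such table. The safety comparison that it does plan covers all AEs, so admissions are included there.

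**Conclusion.** The point holds as a narrowly set definition that is worth widening. It is not an error or a contradiction. A listed admission that is neither life threatening nor fatal is not an SAE under the stated rule. If it is also not deemed related, it falls outside the one-week report and reaches the DMEC Chair as an ordinary AE with no timeframe in the article.

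The size cannot be given, because the article reports no rates of admission, of life-threatening events or of judged relatedness. No effectiveness estimate is affected. The consequence is confined to the speed and clarity of safety reporting.

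The conclusion assumes that the definition and trigger printed in the article are those in force, and that the written procedures not shown do not widen them.

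**What to change.** Class the hospitalisation events already on the AE list as serious for reporting purposes. They would then follow the existing one-week report to the DMEC Chair whatever the judged relatedness, and would be counted by arm as SAEs. The all-AE comparison by allocation can stay as it is.

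This changes reporting only and leaves participants' care untouched. It uses an event type and a route that the protocol already has. The cost is a wording change to the AE form and a small number of extra expedited reports. The article's Discussion describes the AE approach as iterative, so a revision fits the way it is presented.

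Linking the top severity grades to the expedited route would be a further step. It is more debatable, because the grade is itself a judgement, and the point does not depend on it.

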### Public involvement

A panel of young people (drawn from the Young Person’s Advisory Group at the National Children’s Bureau, NCB) and a panel of parents and carers (drawn from the Parent and Carers Advisory Group at NCB) has advised on the development of an appropriate engagement strategy to keep young people (and parents and carers where appropriate) abreast of project developments. The aim is to ensure that the trial explores issues of relevance to young people, and minimises participant attrition. Representatives from both panels have been invited to join the Trial Steering Committee (see below). Panel members include young people who have received training from the NCB Research Centre in a range of research skills (e.g. appraising the academic literature, reviewing engagement materials, co-producing research summaries). We have aimed to involve these panel members at all stages of the study where possible, and look to include them in our dissemination activities where we know that peer feedback is a highly effective way of ensuring that research findings reach the intended audience.

### Governance and oversight

A Trial Steering Committee (TSC) has been established with an independent chair, and representatives from different, relevant professional groups (including a counselling academic, an educationalist, a representative from the ESRC (funder), an independent statistician, and an independent economist), a representative young person and a representative parent/carer, together with members of the research team. The role of the TSC is to monitor the scientific integrity of the trial, the scientific validity of the trial protocol, assessment of the trial quality and conduct as well as for the scientific quality of the final trial report. Decisions about the continuation or termination of the trial or substantial amendments to the protocol are the responsibility of the TSC.

A Data Monitoring and Ethics Committee (DMEC) has also been convened under the direction of an independent chair. The DMEC comprises a clinician, a separate statistician from the TSC, who is also independent of the Trial Management Group (TMG) (see below) and similarly, a separate and independent economist. The role of the DMEC is to review accruing trial data and to assess whether there are any safety issues that should be brought to the participants’ attention, whether any safety amendments should be made or if there are any reasons that the trial should not continue. Open reports are provided to the DMEC by the TMG and closed reports are provided by the CTU. The DMEC Chair reports the DMEC’s recommendations to the Chair of the TSC and may request additional reports or information if required.

A TMG has been established and includes those individuals responsible for the day-to-day management of the trial including the CI, project manager, principal statistician and economist, and all co-researchers. Notwithstanding the legal obligations of the lead organisation (University of Roehampton) and the CI, the TMG has operational responsibility for the conduct of the trial including monitoring overall progress to ensure that the protocol is adhered to, and taking appropriate action to safeguard the participants and the quality of the trial if necessary.

## Discussion

The ETHOS study is the first RCT powered to detect clinically meaningful differences investigating the clinical and cost-effectiveness of SBHC, compared to PCAU. Evidence of the effectiveness of psychotherapeutic interventions with children and adolescents comes mainly from trials of CBT for the treatment of anxiety and depression. As many young people referred to school counselling services are more likely to be experiencing emotional distress as a result of a range of life difficulties, rather than a specific clinical disorder, there is a need for school-based interventions that address these needs. SBHC presents one such potential intervention, and the results from four pilot trials provide preliminary evidence of clinical effectiveness. Determining the clinical and cost-effectiveness of SBHC is important for all stakeholders, including policy-makers, statutory advisory bodies for child welfare, head teachers, children and young people practitioners, child welfare and parenting organisations, and young people.

Conducting the current trial in a school (real-world) setting is a pragmatic approach to assessing the effectiveness of SBHC compared to PCAU, with the added advantage of being able to evaluate the intervention in a way that mirrors routine practice. School pastoral care staff are particularly well placed to identify potentially eligible participants, and so working with schools during the pre-screening period may also be beneficial to the trial’s recruitment rates. A further advantage of conducting the current trial in a school setting pertains to school culture and day-to-day structures (e.g. the use of regular timetables, monitoring of pupil attendance), which lends itself well to scheduling and completing data collection at our four time points.

There are also significant challenges to conducting the current trial within a school context. Necessary protocols for ethical research practice can present a burden to included schools, which are not familiar with the research-related administration involved in running a trial of this size. Equally, the trial’s schedule of time points for data collection and counselling sessions needs to take into account the various academic calendars across schools, including such things as school holidays, site inspections carried out by the Office for Standards in Education, and in-service, school training days for staff. These particular challenges have necessitated training provision and regular debriefing in the research aspects of the trial, with schools; and the nature and realities of school life to our researchers, as well as developing and maintaining strong working relationship between sub-teams. A final challenge of conducting ETHOS in a school environment pertains to the heterogeneous nature of our schools’ pastoral care provision, which may present particular challenges at the point of analysis. We aim to address this challenge through collecting data on each school’s pastoral care provision in the School Characteristic’s Form developed for the study, and by collecting information relevant to each participant’s engagement with their school’s pastoral care services regarding type, regularity and length of time, in a Pastoral Care Log also developed for the study.

In addition, a considerable challenge has included developing a protocol for monitoring and reporting AEs in counselling. The academic literature regarding AE monitoring in RCTs generally relates to trials of pharmacological interventions and there is scant academic literature in the counselling and psychotherapy fields. This has require us to utilise a process of adopting and adapting a model of monitoring and reporting more commonly applied in pharmacological studies, as well as drawing on the clinical expertise within the core research team to inform protocol development. We view our current approach as iterative, and aim towards being able to share an established, more definitive, set of protocols with the counselling research community on trial completion.

A further challenge includes obtaining parent/carer consent prior to the assessment meeting with the young person. While our method of ‘opt-in’ consent was ethically necessary, it can be time consuming to obtain and has presented school staff with additional administrative duties. This has been largely overcome by working closely with school staff as early as possible in the process of identifying young people for the project and engaging their parent/carer. However, this method may also be contributing to the variable recruitment rates we have observed across included schools, as it has required parents and carers to be sufficiently engaged with their child’s school, as well as being able to read English at a sufficient level to understand the Information Sheet for Parents/Carers. Parent/carer ‘opt-in’ consent represents a potential source of selection bias, as we are only including participants who have been willing to involve their parent/carer in their decision to take part in the trial and whose parent/carer has agreed to their involvement; and in terms of only including participants and parents/carers with a sufficient level of English language comprehension.

The results of this trial will contribute significantly to the evidence base for SBHC and to the wider field of adolescent mental health interventions. Our data also has the potential to inform the development of national guidelines for mental health support for schools and make a direct contribution at a policy level, by providing up-to-date and reliable information about the utility of school counselling. A trial that is powered to detect clinically meaningful differences also provides an opportunity to develop an understanding of the process of change in SBHC, and to trial the newly established competency framework for humanistic counselling with children and young people [30]. Furthermore, the research will be used to develop and test a manual for the effective implementation of SBHC by counsellors and psychotherapists.

### Trial status

ISRCTN Registry, ISRCTN10460622 (11 May 2016). The study commenced recruitment in September 2016 and recruitment due for completion in February 2018.

## Abbreviations

AE: Adverse event
BACP: British Association for Counselling and Psychotherapy
BLRI: Barrett-Lennard Relationship Inventory
CBT: Cognitive behaviour therapy
CHI-ESQ: Experience of Service Questionnaire
CI: Confidence interval
CL: Clinical lead
CREST: Centre for Research in Social and Psychological Transformation
CRF: Case Report Form
CSRI: Client Service Receipt Inventory
CYP PRN: Children and Young People Practise Research Network
DMEC: Data Monitoring and Ethics Committee
ES: Emotional Symptoms sub-scale of the SDQ
ESRC: Economic and Social Research Council
ETHOS: Effectiveness and cost-effectiveness trial of humanistic counselling in schools
GBORS: Goal Based Outcome Record Sheet
ICC: Intra-class correlation coefficient
ICER: Incremental cost-effectiveness ratio
ISRCTN: International Standard Randomised Controlled Trial Number
LA: Local Authority
LMM: Linear mixed-effects models
MAHSC-CTU: Manchester Academic Health Science Centre, Trials Coordination Unit
NCB: National Children’s Bureau
NICE: National Institute for Health and Care Excellence
ORS: Outcome Rating Scale
PCAU: Pastoral Care as Usual
PCEPS-YP: Person Centred and Experiential Psychotherapy Scale – Young People
RCADS-SV: Revised Child Anxiety and Depression Scale–Short Version
RCT: Randomised controlled trial
RSES: Rosenberg Self-Esteem Scale
SAE: Serious adverse event
SBHC: School-based humanistic counselling
SD: Standard deviation
SDQ: Strengths and Difficulties Questionnaire
SES: Student Engagement Scale
SMD: Standard mean difference
SPIRIT: Standard Protocol Items: Recommendations for Interventional Trials
SQL: Standard Query Language
TMG: Trial Management Group
TSC: Trial Steering Committee
UK: United Kingdom
UNICEF: United Nations International Children’s Emergency Fund
WAI-S: Working Alliance Inventory – Short Form
WEMWBS: Short Warwick-Edinburgh Mental Well-being Scale
WHO: World Health Organisation
YP-CORE: Young Person’s Clinical Outcomes in Routine Evaluation
